**WHILE ON PREEMPTIVE THERAPY**

- Serum for BDG will be collected every other day until negative. Once the test becomes negative, twice weekly surveillance will be resumed.
- Complete physical examination including vital signs once weekly.
- Assessment for breakthrough IFI as defined by EORTC/MSG criteria.
- LFTs once weekly.
- AEs will be recorded and drug tolerability assessed at the time of the physical examination.
- PAX Gene tubes will continue to be obtained 2 times/week.
- Concomitant medications will be documented weekly.

**END OF PREEMTPIVE THERAPY**

- Clinical response to therapy will be recorded on the CRF (**Table 5)**.
- Subjects will again be assessed for EORTC/MSG criteria for proven or probable IFI.
- Oral wash or ETS for semi-quantitative fungal culture with susceptibility testing.

**EMPIRIC THERAPY**

- Antifungal agent will be documented.
- APACHE II score recalculated based on laboratory and clinical features in preceding 24 hours.
- EORTC/MSG criteria for proven or probable IFI will be determined and documented on the CRF.
- Supporting evidence of IFI obtained as part of routine care will be documented.
- AEs will be recorded weekly.
- Oral wash or ETS for semi-quantitative fungal culture with susceptibility testing will be collected at the beginning and end of empiric therapy.

**FOLLOW-UP (SICU DISCHARGE)**

All study subjects will be followed until SICU discharge or for as long as they are receiving study drug, whichever is longer.

- Assess whether patient has evidence IFI or meets EORTC/MSG criteria for a new proven or probable IFI at SICU discharge.
- Assess mortality at SICU and hospital discharge. Cause of death and date of death will be documented.
- Oral wash or ETS for semi-quantitative fungal culture with susceptibility testing will again be obtained at SICU discharge.

**DIAGNOSTIC TESTS**

Serum for BDG and a PAX Gene tube will be obtained along with the routine morning SICU blood work twice weekly on Monday and Thursday. Samples will be sent to the Duke Clinical Microbiology Laboratory. Serum for BDG will be processed by the study technologist within 6 hours of collection. BDG will be performed by the study technologist and the results reported immediately to the SICU for patients in the active surveillance arm. Serum from patients in the standard care arm will be stored at -70°C and tested at the completion of the study. The BDG assay will be performed as per manufacturer’s instructions, using a positive cutoff of ≥ 60 pg/mL. Other study related laboratory tests (i.e., LFTs) will be performed by the Duke Clinical Laboratories. Blood cultures, surveillance fungal cultures, and susceptibility testing will be performed by the Duke Clinical Microbiology Laboratory as per standard operating procedure. All but the surveillance fungal culture will be reported in the medical record for clinical use. The PAX Gene collection system can remain at room temperature for up to 72hrs, samples will be processed by [name] and all RNA analyses will be performed retrospectively after study completion.

**RNA ANALYSIS METHODS:**

For initial mining of gene expression data, subjects with known positive blood cultures (cases) and those with known negative blood cultures and negative BDG testing (controls) will be selected for initial gene expression studies. RNA will be extracted from PAXgene tubes using standard methodology (RNeasy, Qiagen) and subject to globin reduction (Ambion) by standard methodology. The Duke University Microarray Core will perform quality assurance and hybridization to Operon Human 4.0 Microarrays per standard methodology ([www.microarray.duke.edu](http://www.microarray.duke.edu)). We will then use the decision tree approach to find gene expression patterns that are correlated with candidemia and absence of candidemia to determine the predictive capability of those gene patterns as a diagnostic test.

**DESCRIPTION OF STUDY END POINTS**

**Primary Endpoints**

1. Feasibility of preemptive monitoring strategy.
2. β-D-glucan test performance in the stand care (empiric therapy) group.
3. Safety and tolerability of preemptive anidulafungin.

**Secondary Endpoints**

1. Prevalence of IC by treatment group (i.e., preemptive therapy versus standard care).
2. Duration of SICU stay by treatment group.
3. Number febrile days by treatment group.
4. Antifungal drug utilization by treatment group.
5. Overall mortality rate between treatment arms at SICU and hospital discharge.
6. Response to preemptive or empiric antifungal therapy will be assessed.
7. Fungal colonization rate by group at baseline, at the end of antifungal therapy, and at SICU discharge.
8. Susceptibility of fungal pathogens identified (if any).
9. Number of breakthrough IFIs by group.
10. Number of premature withdrawals from assigned strategy.
11. Costs (antifungal drugs + diagnostic testing) by group.
12. Gene expression signatures related to early candidemia (prior to blood culture positivity) and late candidemia (after blood culture positivity) and no candidemia (negative blood culture and negative B-D-glucan testing).

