**Secondary Objectives**

1. Compare the prevalence of IC between treatment groups (i.e., preemptive versus standard empiric therapy)
2. Compare the duration of SICU stay by treatment group
3. Compare the number febrile days by treatment group
4. Compare antifungal drug utilization between treatment groups
5. Compare the overall mortality rate between treatment arms at SICU and hospital discharge
6. Evaluate clinical response to preemptive or empiric antifungal therapy
7. Compare the prevalence of fungal colonization by group at baseline, at the end of antifungal therapy, and at SICU discharge
8. Determine the susceptibility of fungal pathogens identified (if any) and compare between groups
9. Assess the number of breakthrough IFIs in each management arm
10. Assess premature withdrawals from assigned strategy
11. Compare costs (antifungal drugs + diagnostic testing) between the 2 strategies
12. Obtain RNA from this well-characterized cohort of patients at-risk for the development of IC to derive gene expression signatures that characterize early candidemia

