**Active surveillance/ preemptive therapy group**

Subjects in this arm of the study will have serum drawn twice a week for BDG testing while in the SICU, with the results of the test reported to the managing clinicians in real-time. Subjects will receive intravenous (IV) anidulafungin should the β-D-glucan exceed 60 pg/ml on a single determination. A positive test cut-off of 60 pg/ml was selected based on the observation that 81% of patients with IC will have a positive test at this level(25). Preemptive therapy will continue for a minimum of 14 days or for as long as the subject remains in the ICU up to a maximum of 28 days duration.

If the BDG test turns positive and preemptive therapy is initiated, serum will then be collected every other day to assess the kinetics of the BDG test on anidulafungin treatment. Kinetic monitoring will continue until the test becomes negative at which time twice weekly assessments will be resumed and continue for as long as the patient remains in the SICU. Samples collected while patients are receiving anidulafungin will be batched and run retrospectively. Clinicians will not have these results made available for use in real-time. However, once preemptive anidulafungin therapy is completed and the drug has been stopped, biweekly monitoring with results reported to the medical team will be resumed. Subjects, however will not be restarted on anidulafungin should the test again turn positive after a course of preemptive therapy is completed.

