**Standard care/empiric therapy group**

Patients in the standard care arm will also have biweekly blood draws for the BDG assay until ICU discharge, but the test will not be performed in real-time. Specimens collected from subjects in this arm of the study will be batched and tested retrospectively. The clinicians, therefore, will be blinded to the BDG results and can not use the assay to inform treatment decisions. Because BDG test characteristics in SICU patients are not known, an essential aspect of this study is our ability to assess test performance in the population of interest in an unbiased fashion. Patients in the standard care group may receive antifungal prophylaxis and/or treatment at any time based on the discretion of the treating physician.

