**STATISTICAL METHODOLOGY**

**Sample Size**

Targeted enrollment is 100 adult SICU patients. This study will not be powered to show a difference in the efficacy of preemptive management versus standard care due to single center population constraints in addition to cost limitations. Sample size calculations were therefore based on the number of adult patients expected to be admitted to the SICU over a 1 year period who are likely to meet inclusion criteria (n=700). Based on prior experience, it is reasonable to expect an accrual of 100 patients in a year. Using a 3:1 randomization strategy, 75 will be assigned to active surveillance and 25 to standard care. We estimate that 25% of patients will develop a positive test(13;25;27) and 19 will receive anidulafungin. These numbers should provide sufficient data for a preliminary feasibility evaluation of the preemptive strategy.

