**Data Analysis**

Data Analysis will be performed after completion of data entry, database closure, and verification of database accuracy. All primary and secondary analyses will be performed on the intent-to-treat basis.

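### Colonization is compared by arm at the end of antifungal therapy, a time point that exists only for treated patients, who are selected by a different rule in each arm

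*Protocol*

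**What the plan says.** Item 7 of the Secondary Objectives is to "Compare the prevalence of fungal colonization by group at baseline, at the end of antifungal therapy, and at SICU discharge". Item 7 of the Secondary Endpoints lists the same three time points: "Fungal colonization rate by group at baseline, at the end of antifungal therapy, and at SICU discharge".

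Note e to the Chart of Study Procedures schedules the surveillance culture at baseline, after completion of any systemic antifungal course, and at SICU discharge. The sections on the end of preemptive therapy and on empiric therapy place the end-of-therapy culture within a treatment course; for empiric therapy it "will be collected at the beginning and end of empiric therapy". No matching visit is set for untreated patients.

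The arms start treatment on different grounds:
- **Preemptive arm:** "Subjects will receive intravenous (IV) anidulafungin should the β-D-glucan exceed 60 pg/ml on a single determination".
- **Standard care arm:** "Patients in the standard care group may receive antifungal prophylaxis and/or treatment at any time based on the discretion of the treating physician". BDG results in this arm are withheld from clinicians.

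Under Discontinuation from Study, a preemptive-arm patient started on a systemic antifungal without a positive BDG test or a new proven or probable invasive fungal infection (IFI) leaves the study. The only follow-up stated for such patients is mortality. The Data Analysis section says: "All primary and secondary analyses will be performed on the intent-to-treat basis".

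**The concern.** Randomisation makes the two arms comparable as whole groups. It does not make the treated part of one arm comparable with the treated part of the other when treatment is decided after randomisation by different rules. The end-of-therapy contrast compares exactly those two parts: BDG-positive patients on one side, and patients whom a physician chose to treat on the other.

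The discontinuation rule widens the difference. It removes from the preemptive arm the patients treated on clinical judgement alone, who are the kind of patient that makes up the treated group in standard care.

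Colonization may be linked to either trigger. Table 1 of the protocol lists *Candida* colonization at multiple sites as a risk factor for invasive candidiasis. A gap between arms at this time point could therefore be taken for an effect of the strategy or of anidulafungin when it reflects only who was treated.

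**Working it through.** **1. The protocol's own figure.** Sample Size states: "Using a 3:1 randomization strategy, 75 will be assigned to active surveillance and 25 to standard care", and "We estimate that 25% of patients will develop a positive test(13;25;27) and 19 will receive anidulafungin".
- Allocation: 100 × 3/4 = 75 and 100 × 1/4 = 25.
- Expected preemptive patients treated: 75 × 0.25 = 18.75, rounded up to 19. The figure reproduces.

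**2. Preemptive patients with no end-of-therapy value.**
- 75 − 19 = 56, and 56/75 = 74.7%.
- If the true rate is 25%, the binomial 95% range for the number treated is 12 to 26 of 75.
- The 56 counts BDG-triggered courses only. If 5%, 10% or 20% of BDG-negative patients also received an antifungal (assumed), the share never treated would be 0.75 × 0.95 = 71%, 0.75 × 0.90 = 68% or 0.75 × 0.80 = 60%. The discontinuation rule would take most of these additional patients out of the study.

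**3. Standard care.** The treated share is not stated. If 10%, 20%, 30% or 50% of the 25 are treated (assumed), then 2.5, 5, 7.5 or 12.5 patients contribute.

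**4. What selection alone can do.** Assume no drug effect. Let c be the proportion colonized, the same in both arms, and r the ratio of the chance of being treated in colonized to that in non-colonized patients. Among the treated,

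proportion colonized = c·r / (c·r + 1 − c).

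The treated share cancels. With c = 0.50:

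| r, preemptive | r, standard care | Preemptive | Standard care | Gap (points) |
|---|---|---|---|---|
| 1.5 | 1.5 | 0.75/1.25 = 60% | 60% | 0 |
| 2 | 1 | 1.0/1.5 = 67% | 0.5/1.0 = 50% | +17 |
| 1 | 3 | 50% | 1.5/2.0 = 75% | −25 |

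With c = 0.30 the last two rows become 46% against 30% and 30% against 56%. Neither c nor r is given in the protocol. The table shows only that the sign and size are open, with zero among the possibilities.

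**The case against.** Four points on the other side have force.

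- **Scale.** This is one of three time points of the seventh of twelve secondary endpoints, in a trial that states it is not powered for efficacy. With 19 treated against an assumed 5, the standard error of a 70% versus 50% difference is √(0.21/19 + 0.25/5) ≈ 25 points, so few readers would draw a firm conclusion. This stands and keeps the point minor.
- **No test is named.** Statistical Analyses assigns tests to several endpoints but none to colonization, and a by-group table would satisfy the endpoint wording. The objective, however, says to compare.
- **Intent-to-treat.** A reader might infer that the end-of-therapy comparison contradicts the intent-to-treat statement. That is too strong: treated patients can be analysed in their assigned arm, and an analysis plan could name the population, as the protocol does for response to therapy. Naming a population would still not create cultures for untreated patients or make the treated groups comparable.
- **Discharge is not complete either.** Discontinued patients are stated to be followed only for mortality, and one discontinuation rule applies to the preemptive arm alone. This stands and is carried into the fix.

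A reader might also infer that the Missing Data section condemns the variable, because it rules out imputation and allows a variable missing in 50% of patients to be dropped. The text does not support this. The bar on imputation is limited to the primary analysis, and an end-of-therapy value in a patient who had no therapy is not applicable rather than missing.

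**Conclusion.** The concern holds in a limited form. As written, the objective and endpoint include a between-arm comparison at a time point that about three quarters of the preemptive arm (56 of 75) are expected never to reach. The patients who do reach it are chosen after randomisation by different triggers. That contrast is not randomised and cannot support a statement about the effect of the strategy.

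The three-quarters figure rests on the 25% planning estimate and on counting BDG-triggered treatment only. The corresponding share in standard care cannot be computed.

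It is tempting to attach a direction and an expected size to the bias, for instance that the preemptive arm will look more colonized. The documents do not support this. They give neither a colonization rate nor its association with either trigger. Clinicians in standard care may also respond to colonization, although they do not see the study's surveillance cultures. The gap could be positive, negative or nil.

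Severity: minor. Baseline is unaffected, and SICU discharge is affected only through deaths and patients without a discharge culture.

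**What to change.** Amend item 7 in both Secondary Objectives and Secondary Endpoints:

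1. Base the between-arm comparison of colonization on SICU discharge, by assigned arm, adjusted for the baseline culture.
2. Report by arm the number who died in the SICU and the number without a discharge culture, including patients discontinued under the study's rules.
3. Report end-of-therapy colonization descriptively among treated patients in each arm, as change from the start-of-therapy culture, and label any side-by-side reading as a non-randomised comparison.

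The cultures this needs are already scheduled: baseline and discharge for all subjects, and the start of therapy under the sections on initiation of therapy and on empiric therapy. The change is therefore one of wording. Its cost is that one planned between-arm contrast becomes descriptive. It does not make the discharge comparison complete: obtaining discharge cultures from discontinued patients would require a change to follow-up, and without that the loss can only be reported.

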**END POINT DEFINITIONS**

**Feasibility**

The feasibility of the preemptive monitoring and treatment strategy will be assessed by evaluating adherence to the surveillance protocol in combination with the number of instances where BDG was ordered off schedule to inform treatment decisions and/or systemic antifungal therapy was initiated despite a negative BDG result.

**Invasive Fungal Infection**

The European Organization for Research and Treatment of Cancer/Invasive Fungal Infections Cooperative Group and the National Institute of Allergy and Infectious Diseases Mycoses Study Group (EORTC/MSG) established standard definitions for IFIs for use in clinical research(26). These criteria were designed for immunocompromised patients with cancer and hematopoietic stem cell transplant (HSCT) recipients. Although not developed for ICU patients specifically, these criteria will be applied as a way to standardize the assessments and classification of IFI in study subjects (**Tables 3 and 4**)

**Invasive Candidiasis**

IC will be defined as proven deep tissue *Candida* infection or candidemia.

**Breakthrough Invasive Fungal Infection**

Breakthrough IFIs will be defined as a proven or probable fungal infection that is not present when preemptive or empiric is initiated, but develops and is diagnosed later, after at least 72 hours of antifungal therapy.

**Clinical Response**

Response to empiric therapy will be defined as the resolution of fever and/or other attributable symptoms or signs of IFI after the initiation of systemic antifungal treatment. Response to preemptive therapy will be defined as normalization of the BDG test and resolution of fever and/or other attributable symptoms or signs of IFI (if these were present at the time the BDG test became positive) after the initiation of anidulafungin treatment.

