**Duration of Preemptive therapy**

Preemptive therapy will continue until one of the following occurs:

1. A minimum of 14 days therapy (standard treatment duration for IC and/or candidemia*)*
2. Patient develops a proven or probable breakthrough IFI while receiving study drug (see appendix A for IFI criteria)
3. Patient develops unacceptable toxicity
4. The clinician or PI decides that it is not in the patients best interest to continue
5. Patient declines further study participation
6. Patient has received preemptive therapy for 28 days and has not yet been discharged from the SICU

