**Table 5. Clinical Response**

| **Clinical response*** | **Definition** |
| --- | --- |
| Response to empiric therapy | Resolution of fever and/or other attributable symptoms/signs of IFI |
| Response to preemptive therapy | Resolution of abnormal BDG test result |

*Clinical response as an efficacy endpoint will be assessed at the end of treatment.

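### Clinical response is defined in two conflicting ways, and neither requires freedom from breakthrough infection or survival, so a preemptive treatment failure can count as a response

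*Protocol*

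**What the plan says.** Response to preemptive or empiric therapy is secondary endpoint 6 in the protocol. It is defined in two places.

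- **Clinical Response, empiric arm:** "Response to empiric therapy will be defined as the resolution of fever and/or other attributable symptoms or signs of IFI after the initiation", meaning once an antifungal has been started.
- **Clinical Response, preemptive arm:** "Response to preemptive therapy will be defined as normalization of the BDG test and resolution of fever and/or other attributable symptoms or signs of IFI", with the signs limited by the condition "if these were present at the time the BDG test became positive".
- **Table 5, preemptive arm:** "Resolution of abnormal BDG test result", with no mention of fever or signs. The empiric entry in the table matches the text.

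On timing, the footnote to Table 5 says: "Clinical response as an efficacy endpoint will be assessed at the end of treatment". The section on the end of preemptive therapy agrees: "Clinical response to therapy will be recorded on the CRF". One of the listed ends of preemptive therapy, under Duration of Preemptive therapy, is: "Patient develops a proven or probable breakthrough IFI while receiving study drug".

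Breakthrough IFI has its own definition, an infection absent when therapy began that "develops and is diagnosed later, after at least 72 hours of antifungal therapy". Its count by group is secondary endpoint 9, and mortality is secondary endpoint 5. No section links either one to the response score. Under Statistical Analyses, the response population is everyone with at least 3 days of BDG monitoring and at least one dose of systemic antifungal therapy. Response is determined by the principal investigator and a blinded second investigator.

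**The concern.** A response rate is read as the share of patients treated successfully. Here a breakthrough infection stops preemptive treatment and thereby prompts the response assessment, yet the rule applied at that moment does not look at it. In the preemptive arm the text also restricts attention to signs present when BDG turned positive, so signs of an infection that appears later fall outside the definition.

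Two further problems add to this. The two definitions of preemptive response can classify the same patient differently. In the empiric arm, the and/or wording allows a response when fever has gone but another attributable sign persists.

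At stake is whether the endpoint 6 figures can be interpreted, since some patients counted there as responses may be counted as breakthroughs under endpoint 9.

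**Working it through.** **1. Expected denominator.** From Sample Size: 100 patients randomized 3:1 gives 100 × 3/4 = 75 in the surveillance arm. With 25% expected to test positive, 75 × 0.25 = 18.75, which rounds to the protocol's 19 anidulafungin recipients. The response population could differ slightly because of its 3-day monitoring condition, so 19 is a planning figure. The protocol gives no expected response rate.

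**2. The rules applied to constructed records.**

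| Record | Clinical Response text | Table 5 | Endpoint 9 |
| --- | --- | --- | --- |
| A. Preemptive; no fever or signs at BDG positivity; BDG normalizes; candidemia on day 7 of drug | Response (the signs condition does not apply) | Response | Breakthrough |
| B. Preemptive; fever at BDG positivity, since resolved; BDG normalizes; proven deep-tissue infection on day 10 with new signs | Response (the new signs were not present at positivity) | Response | Breakthrough |
| C. Preemptive; fever the only sign at BDG positivity and persisting; BDG normalizes; no breakthrough | Non-response | Response | None |
| D. Empiric; fever resolves, another attributable sign persists | Response, reading and/or literally | Same | None |

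A and B show the missing breakthrough condition, which has the same effect under either definition. C shows the conflict between the two definitions. D shows the and/or problem, which is separate from breakthrough infection.

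**3. Why A and B reach the assessment.** Both infections appear after more than 72 hours of therapy, so they meet the breakthrough definition. Each ends preemptive therapy, and response is recorded at that point. The response population does not exclude them, and the Data Analysis section puts all analyses on an intent-to-treat basis.

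**4. Size per patient.** In the preemptive arm, one reclassified patient changes the rate by 1/19 = 0.053, or 5.3 percentage points. The protocol does not say how many of the 25 standard-care patients will receive empiric therapy. If all 25 did, one patient would be 1/25 = 4 points. Assuming 10 or 5 treated, it would be 1/10 = 10 or 1/5 = 20 points.

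**5. Total effect.** This would need the frequency of breakthrough IFI and of death on treatment, and the share of those patients who meet the response rule. The protocol gives none of these, so no total is offered.

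**The case against.** **Response is secondary and the failures stay visible.** The protocol says the trial is not powered for efficacy, names no test for response, and reports mortality and breakthrough IFI separately by group. This stands, and it limits the importance of the point. It does not make the response rate interpretable.

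**Two assessors determine response, and an analysis plan may add rules.** Scoring need not be mechanical, and detailed handling of death is often left to an analysis plan. But the protocol does define response, twice, and gives the assessors no criterion for overriding that definition when a breakthrough occurs.

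**The and/or wording can be read as covering whichever signs were present.** That reading is possible. The text does not settle it, and the lenient reading is equally available. In the empiric arm, persisting signs of a new infection could also support non-response, so the breakthrough gap is clearest in the preemptive arm.

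Three stronger readings are tempting but not supported:

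- *A negative BDG alone, or absence of fever alone, always makes a preemptive patient a responder.* Under the Clinical Response text, a patient who had fever or signs at BDG positivity needs BDG normalization as well as their resolution. BDG alone suffices only under Table 5, or when there were no such signs.
- *Patients who die are scored as responders.* Death is not among the listed ends of preemptive therapy, and the classification of a patient who dies before assessment is unstated. Because the primary analysis imputes nothing, the outcome might be treated as missing. Nor is every death in a surgical ICU an antifungal failure; counting all of them as non-response is one convention.
- *The quoted 81% BDG positivity in invasive candidiasis shows how often a breakthrough would be BDG-negative.* It does not. Anidulafungin recipients have already tested positive, and the figure says nothing about their BDG at a later breakthrough on treatment.

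**Conclusion.** The point holds in a limited form. As written, both definitions score a preemptive patient with a breakthrough IFI as a response if BDG has normalized and any signs present at positivity have resolved. The two definitions disagree for preemptive patients whose initial signs persist after BDG has normalized. The empiric rule can be met by fever resolution alone, and the treatment of deaths before assessment is left open.

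The supported size is 5.3 points on the preemptive response rate per affected patient, resting on the protocol's expectation of 19 recipients. How many patients would be affected is unknown. This is a minor-to-moderate correction to a descriptive secondary endpoint. It does not touch the primary endpoints, and deaths and breakthrough infections are still reported in their own right.

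**What to change.** Use a single definition of response in the Clinical Response section and Table 5:

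1. Decide whether preemptive response is BDG normalization alone or BDG normalization plus resolution of signs, and state it identically in both places. The text version is the more complete.
2. Score as non-response, in both arms, any patient with a proven or probable breakthrough IFI by the end of treatment.
3. Replace the and/or wording by resolution of fever and of all other attributable signs present at the start of therapy.
4. Do not count a patient who dies before the end-of-treatment assessment as a responder in the main response analysis. Add a sensitivity analysis in which only deaths attributed to IFI are treated this way; the Statistical Analyses section already plans to summarize attributed mortality.

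The change concerns scoring only, not patient care. Most of the data are already collected: weekly IFI assessments in all subjects, an IFI assessment at the end of preemptive therapy, and date and cause of death. The exception is the empiric arm, where the protocol sets no IFI assessment at the end of therapy and follow-up stops at SICU discharge for patients not on study drug. The definition should therefore say which assessment is used for a patient who leaves the SICU still on empiric treatment. The other cost is a lower stated response rate.
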